### Blind spot mapping

Following the eye tracking calibrations, participants will fixate monocularly (wearing the coloured glasses) at a cross located at the centre of the screen. Fixations will be indicated by changing the orientation of the fixation cross from an upstanding plus sign (i.e., + = fixation; gaze position < 2 DVA away from centre cross) to a 45 degrees rotated plus-sign (i.e., x = no fixation; gaze position > 2 DVA away from centre cross). Participants will be instructed that the cross should remain as an upstanding plus (i.e., +) throughout the task.

Participants will see a small test spot (1 DVA of visual angle) adjacent to the fixation cross. The test spot’s colour (green or red, calibrated per participant) and original position (leftwards or rightwards from cross) will depend on the blind spot mapping that is being performed. As the participant fixates, the researcher will move the test spot along the horizontal axis (Y = 0) away from the fixation cross. Vertical adjustments will also be possible later in the procedure. The participant will indicate when the test spot disappears into their blind spot, at which point the researcher will incrementally enlarge its height (size increase along y axis) and width (size increase along x axis) in small steps until a section of the test spot becomes visible again. The test spot’s location and size will only be adjustable when the eye tracker records a central fixation (i.e., the test spot will be frozen on the screen whenever a missed fixation is recorded). The experimenter will be able to initiate a manual recalibration with a key press (r) in cases where the eye tracker records a missed fixation continuously. These recalibrations will also be employed to give the participant a break when needed. The experiment terminates once the maximum height and width has been established (i.e., any height or width increase or movement of the test spot in any direction would make the test spot visible. The test spot remains invisible as long as the participant fixates centrally). See Fig 2 for an illustration of the procedure.

**Fig 2 pone.0340593.g002:**
[figure not shown]
Blind spot mapping: The experimenter moves a test spot away from fixation along the horizontal axis until the participant reports the stimulus disappearing (i.e., to have entered their blind spot region). The experimenter then increases the width and height of the test spot until the participant’s blind spot is mapped (i.e., any further increase of the height or width of the stimulus would render it visible). The fixation cross changes colour whenever a broken fixation is recorded by the eye tracking equipment. The test spot should become visible when this happens (i.e., blind spot location shifts with gaze). The experiment continues once a fixation is recorded again. Note that while we represent the stimuli in black and white, the real task will use coloured stimuli and will be performed wearing the coloured glasses as shown in Fig 1A. This will allow us to present the stimuli monocularly to either eye depending on the blind spot mapping being performed.

### Main experimental design

Within each task, participants will complete a few training trials and then will engage in runs where stimulation is presented in the left hemifield (LH) and runs where it is presented in the right hemifield (RH). For LH runs, the left eye is ipsilateral and the right eye contralateral, while for RH runs the left eye is contralateral and the right eye ipsilateral. For each hemifield’s run, we will display a patch representing the previously mapped blind spot in the ipsilaterally-permissive colour (which is invisible to the contralateral eye as seen in Fig 1A). We will instruct participants that if the patch becomes visible at any point, or if part of the task-relevant stimulation disappears, it means that they lost fixation and should press a key (‘spacebar’) to abort the trial. Trials will also be aborted automatically whenever a lack of fixation is detected by the eye-tracker. Aborted trials will not be taken into account in data analysis or for staircase procedures (see below), they will be presented again later in the session until a valid response is recorded.

To ensure that dichoptic stimuli are presented at corresponding locations on the left and right retina (i.e., fused), we will present fusion stimuli at the centre-top and centre-bottom of the screen. The fusion stimuli will be vertical 15x3 DVA rectangular arrays (unit square = 0.5x0.5 DVA; distance task, motion curvature task) or horizontal 3x5 DVA rectangular arrays (unit square = 0.5x0.5 DVA; area task) composed of black- and background-coloured squares that will be randomised in arrangement between trials.

### Experiment 1: Distance task

See Fig 3 for a schematic illustration of a single trial of this task. For each trial, we will show participants two pairs of dots sequentially, each for a duration of 0.8s with an overlap of 0.4s. Following the second pair’s disappearance, the fixation will change from a ‘+’ to an ‘x’ to prompt a response. Participants’ task will be to report whether the dots seemed closer to each other in the first or second appearing pair (2-alternative forced choice). Among the two pairs of dots, one, designated as the ‘target’, will always maintain the same distance, while the other, designated as the ‘foil’, will vary around the target distance (possible distance differences range from −3.5 to +3.5 DVA in steps of 0.5 DVA). The order of appearance of target and foil will be decided randomly at the start of each trial.

**Fig 3 pone.0340593.g003:**
[figure not shown]
Distance task: We illustrate two given trials over time (t) in which A. the foil is presented first (above blind spot) for 400 ms, followed by a simultaneous presentation of the foil (above blind spot) and target (spanning blind spot) for 400ms and a presentation of the target alone (spanning blind spot) for 400ms and B. the target is presented first (below blind spot) for 400 ms, followed by a simultaneous presentation of the target (below blind spot) and foil (above blind spot) for 400ms and a presentation of the foil alone (above blind spot) for 400ms. All trials end with a fixation stimulus change from ‘+’ to ‘x’ which cues for a response to the task. Participants’ response is to state which pair of dots had a smaller separation, the one appearing first or second. Note that while we represent the stimuli in black and white, the real task will be coloured and will be performed with the coloured glasses as shown in Fig 1A. This will allow us to present the stimuli either to the contralateral eye or ipsilateral eye.

The target’s fixed dot-distance will be determined for each participant’s hemifield given their individually mapped blind spot area while accounting for dot size, padding to prevent stimuli from breaching the blind spot boundary (+2 DVA for each side of the blind spot – total of +4 DVA) and random jitter to prevent participants from using the retinal eccentricity of the more foveal dots to do the task (−1, −0.5, 0, + 0.5 or +1 DVA, same amount of jitter added to both dots). The distance difference between target and foil for a given trial will be determined by a staircase procedure: when participants select the target as being the smaller distance, the foil distance will decrease by 0.5 DVA for the subsequent trial in the staircase, and when participants select the foil it will increase by 0.5 DVA. For the dot pair spanning the blind spot, both dots are situated on a line including the fixation cross and the centre of the mapped blind spot location. For each trial, both dots are separated from the centre of the blind spot by half the target distance given the random jitter along the radial axis (Dot1 = Blind Spot Center – Target distance/2 + jitter; Dot2 = Blind Spot Center + Target distance/2 + jitter). In the case of the foil, the more central dot and the more peripheral dot of the pair are instead separated by the foil distance. To get the locations for dot pairs that do not span the blind spot, a polar angle representing the height of the blind spot plus 2° rotation is added (above location) or subtracted (below location) vertically to the centre of the blind spot.

We will show both target and foil for each trial either to the ipsilateral or contralateral eye. Crucially, while the foil dot pair will never span the blind spot (presented half the time above or below in a randomised order within a staircase), we will show the target dot pair either spanning the blind spot or not. For each of these combinations, we will define 2 staircases, one for which the foil distance starts as the smallest possible value (i.e., obviously smaller than the target distance) and one for which it starts at the largest possible value (i.e., obviously larger than the target distance). This yields a total of 8 staircases (2 eyes x 2 starting differences x 2 target pair locations) that will run interlaced to compose one run. One staircase procedure ends when it has lasted for at least 30 trials, and there have been at least 10 reversals (defined as a switch from choosing the foil to choosing the target or the opposite). At the start of each trial, one of the staircases that has not already finished will be randomly selected until all staircases are done. A full session of this task including calibration and two runs lasts approximately one hour and a half.

Using these data, we will model psychometric functions relating distance difference between target and foil to the proportion of times the target is chosen as being smaller in distance. These functions will be allowed to vary in terms of bias and precision according to the experimental conditions (around vs not around the blind spot, ipsilateral vs contralateral eye), making it possible to quantify potential disruption of distance perception induced by the blind spot.

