### Operational hypotheses

See Table 1 for a detailed description of each theories’ predictions. In this study protocol, participants will (i) compare the spatial separation between two dot-pairs (to compare distance), (ii) match the area of a circle relative to another (to estimate area size) and (iii) judge the curvature of apparent motion traces (to estimate apparent motion curvature) in trial-based psychophysics tasks. In all three paradigms we compare the accuracy (relating to bias) and precision (relating to slope) of responses to stimulation being presented near the blind spot location or at an eccentrically comparable location away from the blind spot (e.g., above), and for the ipsilateral and the contralateral eye.

**Table 1 pone.0340593.t001:** Table of experimental predictions.

Blind spot (ipsilateral) Predictions about the effect of stimulation around the blind spot on PSE (spatial bias)					
Theory	Decrease	No change	Increase	Confidence	Rationale
IIT	X			Medium	If there is less visual cortex in the blind spot area, it will feel like there’s less visual space in that region (for caveats cf. main text)
NREP	X	X		High	The distance between dots whose rectilinear connection goes through the blind spot, will be inferred by mechanisms using the through-blindspot line information (=incomplete) as well as using the around-blindspot trajectories. The overall estimate may be fully or incompletely corrected for the blind spot gap. Confidence is High that there is no change OR a modest decrease
AI		X		Medium	Perceptual inference reflects unbiased posterior estimate
Predictions about the effect of stimulation around the **blind spot** on **sensitivity (slope)**					
**Theory**	**Decrease**	**No change**	**Increase**	**Confidence**	**Rationale**
IIT	X			Medium	Extra-theoretical considerations suggest that variation in visual quality (btw. stimulated and filled-in qualities) may add to decision variability (a broader psychometric function)
NREP	X	X		Medium	The above ‘conflict’ between through-blindspot and around-blindspot trajectory information may decrease the sensitivity somewhat
AI	X			Medium	Precision estimates will be compromised by reduced information
**Blind spot (contralateral)** Predictions about the effect of stimulation around the **Corresponding Region of Contralateral Eye** on **PSE (spatial bias)**					
**Theory**	**Decrease**	**No change**	**Increase**	**Confidence**	**Rationale**

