### Planned analyses and expected outcomes

Using the data from task 1, we will model the psychometric functions relating the distance difference between target and foil to the proportion of trials the target is chosen as being the smaller distance. Using the data from task 2, we will model the distribution of perceptual area size equivalence across trials. Using the data from task 3, we will model the psychometric functions relating apparent motion curvatures to the proportion of times they are chosen as being curved away from fixation. The resulting models, fitted using a probit link function, will be allowed to vary in terms of intercept (capturing bias effects) and slope (capturing precision effects) according to the experimental conditions (around vs not around the blind spot, ipsilateral vs contralateral eye). Thus, our modelling approach will quantify the potential disruption of spatial perception induced by the blind spot as bias and precision effects for either the ipsilateral or contralateral eye. This modelling approach will be implemented in two ways. We initially use a linear mixed effects model (lme4 package in Rstudio; see [29]), which includes random intercepts for participant and hemifield in addition to the fixed effects of our experimental conditions. This has allowed us to get a first estimate of the effect of eye (ipsilateral eye vs contralateral eye) or location (nearing vs away from blind spot) on the bias and precision of spatial perception while accounting for participant and hemifield response variability.

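### Experiment 1 pools the two presentation orders without an order term, so any preference for the first or second pair flattens the slope that the plan reads as precision

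*Protocol article*

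**What the plan says.** Under the heading Experiment 1: Distance task, participants "report whether the dots seemed closer to each other in the first or second appearing pair". On order, the same section states: "The order of appearance of target and foil will be decided randomly at the start of each trial". The outcome that is analysed is a different variable from the recorded answer, namely whether the target was chosen: "we will model psychometric functions relating distance difference between target and foil to the proportion of times the target is chosen as being smaller".

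Planned analyses and expected outcomes describes the model. It is "fitted using a probit link function, will be allowed to vary in terms of intercept (capturing bias effects) and slope (capturing precision effects"). Both may vary "according to the experimental conditions (around vs not around the blind spot, ipsilateral vs contralateral eye"). The first-stage mixed model is one "which includes random intercepts for participant and hemifield in addition to the fixed effects of our experimental conditions". The section thus names the link, the fixed effects and the random effects. Presentation order is not listed, and no step to check for or remove an interval preference is described.

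Slope is a declared target of prediction. In Table 1 (Operational hypotheses), AI and IIT predict a decrease in sensitivity at the ipsilateral blind spot, and NREP predicts a decrease or no change. AI's stated reason is "Precision estimates will be compromised by reduced information".

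**The concern.** Randomising order protects the PSE, because a shift towards the target on target-first trials is offset by an equal shift away from it on target-second trials. It does not protect the slope. A 50:50 mixture of two shifted curves is shallower than either one. None of the listed terms can absorb this: a participant or hemifield intercept moves both orders the same way, whereas an interval preference reverses sign with order within the same participant.

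An interval preference is not sensory precision, yet the pooled slope counts it as imprecision in every eye-by-location cell. The difference in probit slope between cells, which is what the planned model estimates, is therefore understated. Understatement pushes the result towards no change in sensitivity, which Table 1 allows for NREP at the ipsilateral blind spot but not for AI or IIT.

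**Working it through.** **Design figures from the article.** Staircases per run: 2 eyes × 2 starting differences × 2 target locations = 8, as stated. Each lasts at least 30 trials and 10 reversals, so one eye-by-location cell has at least 2 starts × 2 hemifields × 30 = 120 trials per participant. Distance differences run from −3.5 to +3.5 DVA in steps of 0.5. There are 32 participants.

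**Assumed, because the documents do not give them.** Sensory SD sigma in the control cell: 0.75, 1.0 or 1.5 DVA. Interval preference delta: 0.25 to 1.0 DVA. True SD ratio, blind-spot cell to control cell: 1.30, with 1.25 used in the power check.

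**Formula.** Pooled over order, P(target) = 0.5·Φ((x − μ + delta)/sigma) + 0.5·Φ((x − μ − delta)/sigma). A probit fitted to this has its centre at μ and an SD of about sqrt(sigma² + delta²).

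Example, sigma 0.75 and delta 0.5:
- Control SD: sqrt(0.75² + 0.5²) = 0.901.
- Blind-spot SD: sqrt(0.975² + 0.5²) = 1.096.
- SD ratio: 1.096 divided by 0.901 = 1.22, against a true 1.30.
- Slope difference: 1/0.901 minus 1/1.096 = 0.197, against a true 1/0.75 minus 1/0.975 = 0.308, so 64% is kept.

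**Constant delta, true ratio 1.30** (pooled SD ratio from the formula; share of the true slope difference kept):

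| sigma | delta 0.25 | delta 0.5 | delta 0.75 |
|---|---|---|---|
| 0.75 | 1.27; 88% | 1.22; 64% | 1.16; 42% |
| 1.0 | 1.28; 93% | 1.25; 76% | 1.20; 58% |
| 1.5 | 1.29; 97% | 1.27; 88% | 1.25; 76% |

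**Simulated staircases** (4,000 per setting, half from each start; 30 trials, 0.5 DVA steps, limits ±3.5, order random per trial). With delta at 0.25, 0.5 and 0.75 DVA in turn, the true 30% increase in SD is read by the pooled probit as:
- sigma 0.75: 27%, 19%, 12%
- sigma 1.0: 29%, 25%, 20%
- sigma 1.5: 29%, 27%, 22%

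With an order term the fits return 27% to 31%. At delta 0.5 the share of the effect lost is 11/30 = 37% for sigma 0.75, 5/30 = 17% for sigma 1.0 and 3/30 = 10% for sigma 1.5. A second simulation gave pooled ratios of 1.23, 1.23 and 1.28 at delta 0.5, with 67%, 73% and 89% of the slope difference kept.

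**Power** (32 participants, per-participant probits, paired t-test at two-sided 0.05, true SD 1.00 against 1.25, 60 replicates, Monte Carlo error up to about 6 points):
- delta 0 DVA: 0.95 without order, 0.95 with order
- delta 0.5 DVA: 0.92 without order, 0.98 with order
- delta 1.0 DVA: 0.47 without order, 0.97 with order

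The gap at 0.5 is no larger than the Monte Carlo error; the gap at 1.0 is well beyond it. At delta 0 the order term costs nothing.

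**If delta scales with each cell's noise.** At a preference of one SD (true SD 1.00 against 1.25), the SD ratio stays at 1.25 to 1.27. The raw slope difference still falls, from 0.20 to about 0.15. Power, simulated at SD 1.00 against 1.10, was 0.30 with and without the order term.

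**Standard error of the slope contrast** (32 participants, 6 replicates, delta 0.5). Without order against with order: 0.050 against 0.059 at sigma 0.75, and 0.041 against 0.045 at sigma 1.0. Pooling makes it smaller.

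**The case against.** The strongest reply is that this is an omission, not an error: the article lists the factors of interest and does not exclude further covariates, which an analysis plan or the preregistration may hold. That is possible. But the article does state the model's link, fixed effects and random effects, and that stated model leaves the slope exposed, so the point is an improvement to a model given in the text.

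The size is also open to challenge. No passage suggests a large preference. A delta of 0.5 DVA means choosing the same interval on about 75% (sigma 0.75) or 69% (sigma 1.0) of physically equal trials. The two pairs also share the screen for 400 ms, so this is not a pure memory comparison between intervals. This stands, and is why the size is given only as a range.

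The consequence is limited too. The discussion says the experiment was designed to test IIT's predicted spatial distortion, which is a matter of PSE, and Operational hypotheses attributes IIT's precision prediction to Signal Detection Theory. All three theories predict or allow an ipsilateral slope decrease. This lowers the weight of the point, but slope remains a stated outcome for every theory and is the only ipsilateral change that AI predicts.

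A reader might infer two stronger claims. One is that pooling widens the error bars of the slope contrast; on the probit scale the standard error shrinks, and the estimate shrinks more. The other is that the ratio between cells must move towards 1; that needs a preference roughly constant in DVA, which the documents do not establish.

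**Conclusion.** The point holds in a limited form. For any non-zero interval preference, the model as listed gives slopes that are too shallow and understates the between-cell difference in probit slope. The SD ratio and power are also diluted if the preference is roughly constant in DVA across cells, but not if it scales with each cell's noise. The PSE stays centred apart from chance imbalance in order, and a preference common to all cells creates no false precision difference, so the harm is conservative.

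Under assumed sigma of 0.75 to 1.5 DVA and constant delta, the loss is minor at 0.25 DVA, about a tenth to a third of the precision effect at 0.5 DVA (one staircase step), and larger above that. Neither sigma nor delta is in the documents, so the actual loss in this study is unknown and could be negligible. The change is worth making because it is nearly free.

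**What to change.** Add presentation order (target first = +1, target second = −1) to the Experiment 1 probit model as a fixed effect with a by-participant random coefficient. The by-participant part is needed because preferences may differ in sign and a single common effect could average to zero. Report PSE and slope averaged over the two orders. Put the same term in the likelihood of the Bayesian models, which would otherwise inherit the flattening.

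The cost is one covariate. The program sets order on every trial, so stimuli, trials and sample are unchanged. Data collection is under way, but this touches only the analysis and can be entered as a timestamped amendment by the route in Dealing with amendments.

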### Experiment 2: Area task

See Fig 4 for an illustration of a single trial of this task. For each trial, we will present participants with two circles, one foveally and one peripherally. The location of the foveal stimulus will be fixed around the fixation cross (“fixation” location) with some random jitter (−0.5 to 0.5 in steps of 0.05 DVA, with separate jitter applied to the x and y coordinates relative to the center of the stimulus). The peripheral stimulus will either surround the blind spot (“around blind spot” location) or be at an eccentrically comparable location (“above blind spot” location) with some random jitter (−0.5 to 0.5 in steps of 0.05 DVA, with separate jitter applied to both x and y coordinates relative to the center of the stimulus). Foveal and peripheral stimuli will differ in area. Participants’ task will be to adjust the area of the fixation stimulus to match that of the peripheral stimulus using their mouse. Participants will register the final size selection with a mouse click.

